##### Perspective on costs

This will be undertaken from the NHS and Personal Social Services perspective.

##### Time horizon

This will be the duration over which health outcomes and costs are calculated. The model will use a lifetime time horizon, which will reflect all important differences in costs or outcomes between pharmacogenomic-guided prescribing and standard prescribing in primary care.

##### Outcomes

Quality-adjusted life years (QALYs). QALYs are a measure of the state of health of a person or group in which the benefits, in terms of length of life, are adjusted to reflect the quality of life.

##### Costs

Only direct medical and personal social service costs will be included in the model. Examples of costs to be included are primary care clinicians’ time to consult a patient, laboratory testing costs, test costs, drug costs and alternative drug treatment costs.

### Analytical strategy

A decision analytic model will be constructed for a cohort of typical general practice hosting GPs and non-medical prescribers. The cohort will be modelled over a lifetime. The model will have a structure which reflects a typical patient journey through a GP practice. The model seeks to address the issue of technical efficiency—what is the most efficient model of service delivery, as opposed to allocative efficiency (whether testing is undertaken) and as such, the comparators will be alternative HCPs delivering the service. The intervention will be the use of a pharmacogenomic test to guide prescribing by a prescriber (GP or non-medical). A systematic literature review including existing economic evaluations, randomised controlled trials, observational studies and meta-analyses will be undertaken to inform the inputs of the model. Where there is a gap in the literature, the expert focus group in WS2 will be engaged to inform the inputs in the model. All costs and outcomes will be discounted at 3.5% per annum (as recommended by NICE).

The cost-effectiveness of the new way of working will be calculated using the incremental cost-effectiveness ratio, which is the difference in costs between the intervention and standard care divided by the difference in effect between the intervention and standard care. This will be compared with NICE thresholds for cost-effectiveness.

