### Aims and objectives

This study aims to investigate the perceived barriers and facilitators to the implementation of pharmacogenomic testing in the UK primary care setting. Furthermore, it seeks to assess the value of implementing such testing when led by GPs, pharmacists or nurses.

This study is divided into three workstreams (WS) with the following objectives:

**WS1**—To explore the views of UK patients and HCPs, which includes GPs, practice pharmacists, community pharmacists and practice nurses, regarding the perceived barriers and facilitators for the implementation of pharmacogenomics into routine primary care practice, using the Consolidated Framework for Implementation Research (CFIR).**WS2**—To build on the findings of WS1 to develop pharmacogenomic-guided clinical pathway(s)/workflow(s). HCPs with expertise in genomics and patients will consider the operational changes for implementation, as well as the division of roles and responsibilities through relevant stakeholder engagement.**WS3**—To estimate the cost-effectiveness of implementing pharmacogenomic testing in primary care led by GPs, pharmacists or nurses.

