**Figure 1 F1:**
[figure not shown]
Displays some exemplar pharmacogenomic-guided clinical pathways. GP, general practitioner.

A review of the literature will be conducted to identify the proposed process steps, such as pretest counselling, ordering the pharmacogenomic test and actions based on the test results. Once the process steps are mapped out, a matrix will be developed to categorise various pharmacogenomic testing models based on the HCP leading the process (eg, GP-led, pharmacist-led, nurse-led).

A decision-analytic model will be developed in Microsoft Excel to compare the cost-effectiveness of the pharmacist-led, GP-led, nurse-led or multidisciplinary approaches. This model will align with the National Institute for Health and Care Excellence (NICE) technology evaluation methods.^25^

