##### Comparator

Standard prescribing practices in primary care, where prescribing is undertaken by a GP without pharmacogenomic guidance.

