### Sensitivity analyses

Sensitivity analyses^26^ will be performed. Deterministic sensitivity analyses will be used to determine variation for a set of parameters. This will involve varying the model input values and recording the impact of these changes on the model outputs. Probabilistic sensitivity analyses will be used to characterise the joint distribution of uncertainty in costs and QALYs. The outputs will be reported in terms of the probability of each pathway being cost-effective.

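### WS3 asks which delivery model is most efficient, but its only ICER rule compares with prescribing without testing, so it answers the question the plan sets aside

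*Protocol article*

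**What the plan says.** All references are to the protocol article.

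- **Question.** Analytical strategy presents the issue as technical efficiency: "what is the most efficient model of service delivery, as opposed to allocative efficiency (whether testing is undertaken").
- **Comparator, first statement.** The same sentence goes on to say that "the comparators will be alternative HCPs delivering the service".
- **Comparator, second statement.** The Comparator section reads "Standard prescribing practices in primary care, where prescribing is undertaken by a GP without pharmacogenomic guidance". The Time horizon section is framed the same way, by differences between guided and standard prescribing.
- **Decision rule.** The last paragraph of Analytical strategy defines one ICER, "the difference in costs between the intervention and standard care divided by the difference in effect between the intervention and standard care", and adds: "This will be compared with NICE thresholds for cost-effectiveness". No threshold value is given.
- **Options.** The text after Figure 1 says the model will "compare the cost-effectiveness of the pharmacist-led, GP-led, nurse-led or multidisciplinary approaches", which is four pathways. The WS3 objective under Aims and objectives has three: "To estimate the cost-effectiveness of implementing pharmacogenomic testing in primary care led by GPs, pharmacists or nurses".
- **Probabilistic output.** Sensitivity analyses ends: "The outputs will be reported in terms of the probability of each pathway being cost-effective". It does not say relative to what.

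**The concern.** The two comparator statements describe different analyses. If the question is which professional should lead the service, the relevant increments are those between pathways. If the comparator is prescribing without a test, the increments measure the value of testing as delivered by each pathway. The article says it wants the first and then writes the formula for the second.

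A threshold test against a common baseline is a pass/fail test applied to each pathway separately. More than one pathway can pass, and the rule has no step for choosing among those that do. Ordering the pathways by their ICERs against standard care is not a safe substitute, because a pathway with a higher ratio may gain enough extra QALYs to be the better choice at the threshold.

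The Discussion says the economic results should inform implementation and the allocation of resources. A statement that several pathways are acceptable against no testing would not tell a commissioner which one to set up. The probability output has the same weakness if it is calculated one pathway at a time against standard care.

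**Working it through.** The article gives no WS3 cost, QALY, ICER or threshold, so there is no figure of its own to reproduce. The check tests the logic of the rule on assumed inputs.

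**Assumed increments over standard prescribing (none from the article)**

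| Pathway | Cost (£) | QALY |
|---|---|---|
| Nurse-led | 60 | 0.005 |
| Pharmacist-led | 100 | 0.010 |
| GP-led | 200 | 0.016 |
| Multidisciplinary | 290 | 0.018 |

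**Step 1: the stated rule.** ICER = incremental cost / incremental QALY, both against standard prescribing.

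- Pharmacist-led: 100 / 0.010 = £10,000
- Nurse-led: 60 / 0.005 = £12,000
- GP-led: 200 / 0.016 = £12,500
- Multidisciplinary: 290 / 0.018 = £16,111

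All four pass at any threshold above £16,111.

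**Step 2: value at a threshold.** Net benefit = threshold × QALY gain − incremental cost. At an assumed £20,000 per QALY:

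- GP-led: 320 − 200 = £120
- Pharmacist-led: 200 − 100 = £100
- Multidisciplinary: 360 − 290 = £70
- Nurse-led: 100 − 60 = £40

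The lowest ICER belongs to pharmacist-led, the highest net benefit to GP-led.

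**Step 3: fully incremental analysis.** Nurse-led costs £12,000 per QALY against standard prescribing, but the next step, to pharmacist-led, costs only (100 − 60) / (0.010 − 0.005) = £8,000. Nurse-led is therefore extendedly dominated. The remaining steps are:

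- Pharmacist-led v. standard prescribing: £10,000
- GP-led v. pharmacist-led: 100 / 0.006 = £16,667
- Multidisciplinary v. GP-led: 90 / 0.002 = £45,000

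**Step 4: range of thresholds.** On these inputs, pharmacist-led is preferred from £10,000 to £16,667, GP-led from £16,667 to £45,000, and multidisciplinary above that. At £10,000 no pathway has positive net benefit.

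**Step 5: when the orders agree.**

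- *Equal QALYs.* With 0.010 QALY in every pathway and costs of £80, £100, £150 and £190, the ICERs are £8,000, £10,000, £15,000 and £19,000. This is the cost order and also the order of value.
- *Unequal QALYs.* Agreement is possible here too. Assumed increments of £100/0.0100, £115/0.0105, £150/0.0105 and £180/0.0110 (nurse-led, pharmacist-led, GP-led, multidisciplinary) give ICERs of £10,000, £10,952, £14,286 and £16,364. Net benefits at £20,000 are £100, £95, £60 and £40, in the same order. All four still pass the stated rule.

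**Step 6: the two readings of the probability.** This simulation used 200,000 draws around the tabulated inputs at £20,000 per QALY. Costs were normal with SD 15% of the mean. QALYs had a shared relative uncertainty with SD 25% (0.003 / 0.012) and pathway-specific noise with SD 0.0015.

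| Option | P(cost-effective v. standard prescribing) | P(best of all five options) |
|---|---|---|
| Pharmacist-led | 0.95 | 0.28 |
| GP-led | 0.91 | 0.51 |
| Nurse-led | 0.84 | 0.04 |
| Multidisciplinary | 0.75 | 0.16 |
| Standard prescribing | – | 0.02 |

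The first column sums to 3.45 and puts pharmacist-led on top. The second is a probability distribution over the options and puts GP-led on top.

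**The case against.** The strongest reply is that the ICER sentence is a generic definition in a condensed article. The plan does say it will compare the pathways, it names alternative professionals as comparators, and it commits the model to NICE technology evaluation methods. Dominance handling and net-benefit reporting could sit in a fuller document. The same model outputs would support a full ranking at any time, so nothing is lost irrecoverably.

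Part of this stands. Missing detail on dominance or simulation structure would not be a finding by itself. But condensation does not explain two different comparators and an explicit formula that follows the one at odds with the stated question, and a general commitment to NICE methods does not override that formula.

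Three stronger readings are tempting but not supported:

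- **That the planned analysis cannot rank the pathways at all.** The limit lies in the ICER-against-threshold rule. Under equal QALYs, and in the second unequal-QALY example above, the ICERs order the pathways correctly. The probability sentence can also be read as a probability across all options, which would rank them.
- **That all four pathways will be reported as cost-effective.** The rule allows this. Without any cost or QALY figures, nothing shows that it will happen.
- **That QALY differences between pathways will be near zero, making ratios between them unstable.** The article does not say so. If it were true, ICERs against standard care would come close to ordering the pathways correctly by cost.

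**Conclusion.** The contradiction is in the text and depends on no assumed number: the question and one comparator statement concern pathways against each other, while the Comparator section, the Time horizon section and the only ICER rule concern testing against no testing. As written, the rule answers the excluded question, can pass several or all pathways, and has no step for choosing among them.

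The effect on this study cannot be quantified. The reversal between pharmacist-led and GP-led (£10,000 v. £12,500 by ICER, £100 v. £120 by net benefit) shows what can happen when QALYs differ between pathways, on assumed inputs and an assumed threshold of £20,000 per QALY. It is not a prediction. The point should be fixed before WS3 reports, but it does not invalidate the model, whose outputs could be analysed correctly without being rebuilt.

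**What to change.** 1. Reconcile Aims and objectives, Comparator, Time horizon and Analytical strategy to one decision set: standard prescribing plus the GP-led, pharmacist-led, nurse-led and multidisciplinary pathways. This also adds the multidisciplinary pathway to the WS3 objective.
2. Replace the single ICER rule with a fully incremental analysis: order the options, remove those that are dominated or extendedly dominated, and compare each remaining option with the next best. Net benefit at a stated threshold is equivalent for the decision; which of the two leads the report is a matter of preference.
3. Under Sensitivity analyses, define the reported probability as the probability that each option is the most cost-effective of all options in the set.
4. ICERs against standard prescribing may still be reported, labelled as the value of testing under each pathway.

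The cost is protocol wording and a few spreadsheet columns. No new data are needed.

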### Sensitivity analyses

Sensitivity analyses^26^ will be performed. Deterministic sensitivity analyses will be used to determine variation for a set of parameters. This will involve varying the model input values and recording the impact of these changes on the model outputs. Probabilistic sensitivity analyses will be used to characterise the joint distribution of uncertainty in costs and QALYs. The outputs will be reported in terms of the probability of each pathway being cost-effective.

## Discussion

This study will provide valuable evidence into the perspectives of both HCPs and patients on the use of pharmacogenomic testing in the primary care setting in the NHS, an area where current evidence remains limited. It will also explore the implementation of pharmacogenomic testing through clinically plausible, HCP-led pathways to assess their practicality, feasibility and cost for use in primary care.

In addition to capturing stakeholders’ views, the study will also generate economic evidence concerning the integration of pharmacogenomic testing into routine practice. This cost-effectiveness analysis will be particularly informative for decision-makers, offering them essential evidence to guide future implementation strategies and resource allocation.

### Study limitations

One of the main limitations of this study is that the sampling, data collection, coding, analysis and interpretation will be undertaken by the main researcher, but guided and supervised by the research team. The main researcher, as a practising pharmacist and woman of colour, brings her own inherent biases into the way the research is conducted. However, with the aid of a strong supervisory team, these biases may be limited. In terms of representation of participants, efforts will be made to include a wide cohort, representing different voices across the HCPs, ages, genders and ethnicities. However, participants in this study will be those that are interested in the research topic and may not be reflective of the general population. This study focuses on the primary care setting in the NHS, a health service which is publicly funded and therefore its applicability to other healthcare settings will be limited.

### Ethics and dissemination

The NHS Health Research Authority and Health and Care Research Wales (24/PR/1088) have approved this study protocol. All participants will receive written study information about the purpose of the study, background information about pharmacogenomic testing and the consent form. Results from this study will be presented at scientific meetings. Publications will be through a written doctoral thesis and journal publications, and conferences. Findings will be disseminated to NHS England/Genomics England. Participants will not be identified in any publication. This study is part of an educational qualification for a PhD. A summary of the study will be provided to the funder.

### Patient and public involvement

This study was presented to a patient and public panel. The panel was supportive of the study, with the consensus that pharmacogenomics could help with particularly difficult-to-treat patients, especially those who had polypharmacy. Further, I have a PPI member who has and will continue to be involved in the study.
